## Abstract

**Background:**

Cognitive side-effects are an important reason for the limited use of electroconvulsive therapy (ECT). Cognitive side-effects are heterogeneous and occur frequently in older persons. To date, insight into these side-effects is hampered due to inconsistencies in study designs and small sample sizes. Among all cognitive side-effects, confusion and delirious states are especially troublesome for patients, relatives and clinicians. In particular inter-ictal delirium-like states are worrisome, since they may lead to premature treatment discontinuation. Besides a need for further insight into determinants of cognitive side-effects of ECT, there is a great need for treatment options.

**Methods and design:**

The Rivastigmine for ECT-induced Cognitive Adverse effects in Late Life depression (RECALL) study combines a multicenter, prospective cohort study on older patients with depression, treated with ECT, with an embedded randomized, placebo-controlled cross-over trial to examine the effect of rivastigmine on inter-ictal delirium. Patients are recruited in four centers across the Netherlands and Belgium. We aim to include 150 patients into the cohort study, in order to be able to subsequently include 30 patients into the trial. Patients are included in the trial when inter-ictal delirium, assessed by the Confusion Assessment method (CAM), or a drop in Mini Mental State Examination (MMSE) score of ≥4 during ECT, develops. In the cohort study, comprehensive measurements of ECT-related cognitive side-effects—and their putative determinants—are done at baseline and during the ECT-course. The primary outcome of the clinical trial is the effectiveness of rivastigmine on inter-ictal delirium-severity, assessed with a change in the Delirium Rating Scale-Revised-98. Secondary outcomes of the clinical trial are several ECT-characteristics and side-effects of rivastigmine.

**Discussion:**

This study is the first clinical trial with a focus on ECT-induced, inter-ictal delirium. The cohort provides the basis for recruitment of patients for the cross-over trial and additionally provides an excellent opportunity to unravel cognitive side-effects of ECT and identify putative determinants. This paper describes the rationale and study protocol.

**Clinical trial registration:**

EudraCT 2014-003385-24.

## Introduction

Electroconvulsive therapy (ECT) is considered safe and the most effective treatment for major depressive disorder (1). Despite these qualifications, the use of ECT in clinical practice around the world is limited. This can be attributed to, amongst others, fear of cognitive side-effects, which include amnesia, confusional- or delirious states (e.g., postictal disorientation/-agitation, and prolonged postictal delirium or inter-ictal delirium), and other non-memory cognitive side-effects (e.g., executive function disorder) (2–6). Cognitive side-effects are common in ECT-patients, with 41% reporting anterograde memory impairment, confusion in 37%, and post-ECT delirium in 5.7–12% of patients (7–11). To date, insight into these side-effects is hampered due to a lack of consensus on cognitive testing during and after ECT and variable ECT techniques across studies. This resulted in large heterogeneity in (timing of) outcome measures between studies (12, 13).

Of all studies on cognitive side-effects in ECT, studies on delirious states following ECT have been relatively sparse, in comparison to, for example, memory related side-effects (5, 10). This is troublesome, as especially the inter-ictal (or prolonged post-ictal) delirious states (henceforth called inter-ictal delirium) greatly burden patients and their relatives, and are an important reason to (prematurely) stop ECT, resulting in failure to achieve remission. As ECT is often the last treatment option for severe depression, failure to achieve remission with ECT may lead to persistent loss of quality of life, institutionalization, and high societal costs. It is currently not known how to treat inter-ictal delirium, as non-medication interventions, benzodiazepines, and antipsychotic medication are seldom effective. However, some reports have shown promising results for (acetyl)cholinesterase inhibitors (AChI) to treat inter-ictal delirium specifically (6, 14).

The rational to supplement acetylcholine in the treatment of post-ictal delirium is based on the hypothesis that changes in acetylcholine levels could be associated with cognitive side-effects of ECT (15). This may particularly involve older persons, considering changes in cholinergic signaling in the aging brain (16). Additionally, a lack of acetylcholine—the most important neurotransmitter of the cholinergic system—is thought to be one of the important causes of delirium in general (17). It is known that ECT initially causes an ictal peak of acetylcholine and postictal (e.g., post-ECT) drop of acetylcholine, mediated by cholinesterase (15, 18, 19). In 2015, van Schaik et al. published a case-series describing the putative beneficial effect of transdermal rivastigmine on ECT-induced cognitive side-effects in older ECT patients (8). Hence, a systematic review was done to examine the effect of (acetyl)cholinesterase inhibitors (AChI) (e.g., rivastigmine, donepezil, galantamine) to reduce cognitive side-effects of ECT (20). This systematic review by Henstra et al., included 5 clinical trials which all showed a positive effect of AChI on cognitive tests, but none of these studies studied the post-ECT delirium or inter-ictal delirium.

The primary objective of this study is to investigate in a multicenter, randomized, double-blind, placebo-controlled cross-over trial, whether rivastigmine can be used as a novel treatment to treat ECT-induced inter-ictal delirium in older persons. Additionally, we aim to investigate side-effects of rivastigmine, including its effects on ECT parameters and anesthesia-induced muscle relaxation. In order to detect persons with inter-ictal delirium who are eligible for the trial, longitudinal follow-up of persons treated with ECT is needed. Therefore, we embedded the trial in a cohort study. In this cohort study, comprehensive measurements of ECT-related cognitive side-effects—and their putative determinants—are done to gain insight into the broad palette of cognitive side-effects of ECT.

## Methods and analysis

In line with the SPIRIT (Standard Protocol Items: Recommendations for Interventional Trials) guidelines, we provide information on scientific background, the rationale and objectives, the design and methodology of this study (21).

### Study design and research setting

The RECALL study combines a multicenter, prospective cohort study on older patients with depression who are referred for ECT to study the broad palette of cognitive side-effects (and their determinants), with an embedded cross-over trial to examine rivastigmine as a treatment option for patients with inter-ictal delirium (see Figure 1 for a schematic overview of the RECALL study). The trial is designed as a randomized, double blind, placebo-controlled, cross-over trial. Patients are recruited at four mental healthcare institutes; (1) GGZ inGeest (partner-institution of Amsterdam University Medical Center, formerly VU University Medical Center), Amsterdam, The Netherlands, (2) Parnassia Psychiatric Institute, The Hague, The Netherlands, (3) OLVG-West, Amsterdam, The Netherlands, and (4) UPC KU Leuven, Leuven, Belgium. GGZ InGeest, and Parnassia Psychiatric Institute are general mental healthcare institutes; OLVG West is a general hospital with a psychiatric ward, and UPC KU Leuven is an academic hospital.

**Figure 1 F1:**
[figure not shown]
Schematic representation of RECALL study.

### Study population and inclusion criteria

In- and outpatients, aged 55 years or older, fulfilling the Composite International Diagnostic Interview CIDI) criteria of a Major Depressive Episode—in the context of a unipolar major depressive disorder or bipolar disorder- and referred for ECT-treatment, are asked to participate in the cohort and, in case of occurrence of inter-ictal delirium, in the trial (22–24). Before inclusion, they provide a written informed consent form. The presence of an inter-ictal delirium is examined with the Confusion Assessment Method (25) (CAM) and/or Mini Mental State Examination (26) (MMSE), administered by a trained research assistant. For a diagnosis of inter-ictal delirium, patients need to have a CAM score indicating delirium or a drop in MMSE-score of at least 4 points as compared to baseline. The evaluation of inter-ictal delirium was done during regular screening once weekly, preferably in the middle of a week, 1 day (and maximum 2 days) after ECT. This timing was chosen to (1) select persistent cases of delirium, and hence not to include mild disorientation or transient delirious episodes immediately post-ECT; (2) to increase feasibility by avoiding cognitive testing during weekends and (3) to diminish the learning effect of repeated cognitive testing. Once delirium was diagnosed, an evaluation was done by the clinician to indicate whether it was needed to further exclude possible causes of delirium.

### Exclusion criteria

Exclusion criteria for participation in the cohort study are comorbid somatic conditions that are a relative contraindication for ECT, according to the prevailing Dutch ECT-guidelines, e.g., recent (within 3 months) myocardial infarction or cerebrovascular accident, a diagnosis of neurocognitive disorder, insufficient command of the Dutch language and prior participation in the cohort study (27). Additional exclusion criteria for participation in the trial are: diagnosed (treatable) somatic causes of delirium other than ECT (e.g., urinary tract infection) and contra-indications for rivastigmine use, such as bradycardia or atrio-ventricular (AV) conduction disorder (first degree AV-block excluded), current use of a AChI or a known allergic or adverse reaction to rivastigmine. As it is a cross-over trial, each cross-over patient serves as his or her own control. Since large, intercurrent changes in individual patients' situation hamper a cross-over comparison, patients who switch from (right) unilateral electrode placement (RUL) to bilateral electrode placement (BL), or individuals who receive dose adjustments of antipsychotics during the trial will be marked as drop-outs. Notably, participation in the cohort can be continued when patients drop out due to trial specific exclusion criteria.

### Recruitment

When ECT is indicated (for depression) and the patient is referred by the treating psychiatrist, the patient is subsequently informed on the study and protocol. This information is provided by the treating physician or a trained research assistant, both orally and with a patient information letter. Next, the patient is given 24 h to consider participation in the study, before written informed consent (for the cohort and if eligible for the trial) is obtained from each patient or legal representative (available upon request, notably the informed consent form is written in the Dutch language). The consent can be withdrawn at any time without citing reasons and without any consequences for the treatment. There is no financial incentive for the patient. The duration of inclusion is estimated at ~4 years. Promotional materials, including a folder and posters, have been developed and are available upon request.

### ECT procedure

ECT is given twice weekly. Electrode placement is decided by the ECT team, in accordance to Dutch ECT-guidelines (27). A course starts preferably with right unilateral stimulation (RUL), but bilateral stimulation (BL) is also allowed. Seizures are induced using the Thymatron system IV, Somatics, Lake Bluff, Illinois, USA, (maximum energy 200%, 1,008 millicoulombs) or the SpeECTrum 5000 Q, MECTA corp., Tualatin, Oregon, USA (max energy 200 J, 1,152 millicoulombs). Considering the interaction with seizure quality, we aim to discontinue lithium and other mood stabilizers at least 3 days before ECT starts. For the same reason, we aim to taper down benzodiazepines to a maximum of 30 milligrams oxazepam or 10 milligrams diazepam 3 days prior to the start of ECT. Antipsychotics and antidepressants may be continued and their use is recorded at each ECT-session. Anesthesia is induced with intravenous etomidate (±0.25 mg/kg) or propofol (±1 mg/kg) and muscle relaxation with succinylcholine (1–2 mg/kg). Patients are ventilated with 100% oxygen during the procedure in order to obtain hyperoxygenation status. The oxygen saturation (SpO_2_) level is kept above 95% in the pre-treatment phase. The ECT team performs a stimulus-titration procedure in the first session to determine the seizure threshold. The electroconvulsive treatment goal is set at six times the seizure threshold, brief pulse (0.5–1.0 ms), for RUL ECT, and 1.5–2.5 times seizure threshold for BL ECT. The ECT course is terminated when the patient reaches remission, defined by a Montgomery Åsberg Depression Scale score (28) (MADRS) of ≤ 10/60 during two consecutive weeks, when intolerable side-effects occur, or when no improvement occurs for 2 weeks after a full course of ECT is provided [maximum of six sessions of RUL ECT and six sessions of BL ECT (in total 12 sessions)].

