### RECALL trial: Treatment allocation, intervention, and blinding

After inclusion in the trial, randomization is organized with a two by two Williams design (29). Block randomization is performed by the pharmacy department of the Amsterdam University Medical Center—location VUmc, with stratification for each site. Patients are randomly assigned to either the rivastigmine-followed-by-placebo group, or the placebo-followed-by-rivastigmine group. Each treatment arm lasts for four consecutive ECT sessions (Figure 1). Except for the unblinded nurse or research assistant (i.e., nurse or research assistant who is not involved in other parts of the study, nor in clinical practice, but only applies the patches), all other study members are blinded. “Trial treatment randomization lists” with codes are provided by an independent pharmacist and will only be available for the unblinded nurse or research assistant who applies the patches. Rivastigmine patches delivering 4.6 mg/24 h (Hexal AG, Holzkirchen, Germany) and Hansaplast® placebo patches (of similar size) are labeled in accordance with EU GMP annex 13 regulations and supplied to the sites. To improve and monitor adherence to the trial protocol, drug accountability lists are filled in. The Tmax of rivastigmine patches is 10–16 h, therefore the application of the rivastigmine (and placebo) patches is done the evening prior to ECT. The patch is removed after 24 h. As previously mentioned, during the trial, co-medication is allowed and there are no restrictions to clinical care as usual. As specified in the exclusion criteria however, patients with adjustments in antipsychotic medication or in electrode placement, are excluded from the trial. Benzodiazepines are allowed (e.g., in cases of profound agitation or insomnia). All changes in medications during the trial are registered after every ECT-session. Prior to each ECT-session, side-effects of rivastigmine are assessed, and in case of serious side-effects (e.g., gastrointestinal adverse reactions such as severe nausea), the participation in the trial will be stopped and rivastigmine discontinued. In case of persistent side-effect after discontinuation, the clinician will treat the patient according to the clinical picture (e.g., anti-emetics in case of nausea).

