### Outcome measures

Table 1 shows a full summary of patient characteristics and outcome measures, including the time of collection.

**Table 1 T1:** Collection of patient characteristics and outcome measures in the RECALL trial and cohort.

	**Baseline**	**Regular care**		**Trial**							**Regular care in cohort**		
		**in cohort**									**after finishing the trial**		
	**Baseline**	**Max 90 minutes after ECT**	**Once a week during ECT** ^∧^	**Day before first ECT**	**Max 90 minutes after first ECT**	**Max 90 minutes after 2**^nd^ **ECT**	**Day after 2**^nd^ **ECT**^∧^	**Max 90 minutes after 3**^rd^ **ECT**	**Max 90 minutes after 4**^th^ **ECT**	**Day after 4**^th^ **ECT**^∧^	**Max 90 minutes after ECT**	**Once a week during ECT** ^∧^	**1 week after stop ECT**
Time	Ta	Tb		T0	T1	T2	T3	T4	T5	T6	Tb		
Socio-demographics	X												
*General clinical-demographics*													
Medical history	X												
Substance use	X												
Medication use	X	X		X	X	X		X	X	X	X		X
ATHF	X												
BMI	X												
Waist circumference	X												
Blood pressure	X												
*Physical activity and frailty*													
Frailty index	X												X
SPPB	X												X
Physical activity*	X												
Vision and hearing ability	X												
*Depression related clinical characteristics*													
BAI^a^	X												
GDS^a^	X												
AES^a^	X			X			X			X			X
MADRS^a^	X		X				X			X		X	X
CORE	X		X				X			X		X	X
*Neurocognitive characteristics*													
Battery of neuropsychological tests**	X												X
Self reported cognitive decline	X												X
IQCODE	X												X
(f)MRI	X												
EEG	X												
*Laboratory characteristics*													
Blood / urine sample	X			X									X
*Primary outcome measure*													
DRS-R-98				X	X	X	X	X	X	X			
*Secondary outcome measures*													
MMSE	X		X				X			X		X	X
Letter fluency	X			X			X			X			X
Clock Drawing Test	X			X			X			X			X
Reorientation time		X			X	X		X	X		X		
RASS		X			X	X		X	X		X		
CAM		X	X										
ECT characteristics		X			X	X		X	X		X		
Rivastigmine side-effects				X	X	X		X	X	X			

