
Furthermore, in order to investigate the safety and effect of rivastigmine on ECT-parameters and anesthesia, we measure blood pressure, peak heart rate, seizure length (EEG and motor duration in seconds), postictal suppression index (in %) and seizure threshold. Apart from the postictal suppression index and seizure length measured by the Thymatron IV (unavailable at sites with the spECTrum), all variables are recorded by a blinded anesthesiologist. Next, side-effects of rivastigmine are evaluated twice weekly (by a research assistant) using a four-point side-effects scale with the five most common side-effects of rivastigmine (nausea, vomiting, diarrhea, abdominal pain, allergic skin reaction), and an open question for additional side-effects.

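### Seizure threshold and muscle relaxation are named as rivastigmine safety questions without a described within-trial measurement, and side-effects are rated the day after period 2 but not period 1

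*Protocol article*

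**What the plan says.** The Introduction gives the safety aim: "we aim to investigate side-effects of rivastigmine, including its effects on ECT parameters and anesthesia-induced muscle relaxation".

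Under Secondary outcome measures, the list offered for ECT parameters and anesthesia is: "we measure blood pressure, peak heart rate, seizure length (EEG and motor duration in seconds), postictal suppression index (in %) and seizure threshold". Table 1 schedules a row for ECT characteristics at T1, T2, T4 and T5, that is, after each of the four trial ECT sessions.

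On threshold, the ECT procedure section says: "The ECT team performs a stimulus-titration procedure in the first session to determine the seizure threshold". Trial entry comes after the ECT course has begun: the Abstract requires delirium on the CAM, "or a drop in Mini Mental State Examination (MMSE) score of ≥4 during ECT, develops".

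The Table 1 row "Rivastigmine side-effects" is marked at T0, T1, T2, T4, T5 and T6, and the T3 cell is empty. The treatment allocation section says: "Prior to each ECT-session, side-effects of rivastigmine are assessed". Secondary outcome measures gives a frequency of twice a week. The Harms section has all spontaneously reported or observed adverse events in the trial recorded.

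The primary outcome section closes the first period at T3 and the second at T6. Data analysis gives each treatment two ECT sessions and seven days. The treatment allocation section gives each arm four sessions.

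**The concern.** A secondary safety question needs a measurement taken under each treatment. Two of the named quantities do not appear to have one. A threshold fixed before randomisation is a patient characteristic and carries no information on treatment. An aim with no measure ends without a result.

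The side-effect schedule raises a different problem. The patch goes on the evening before ECT and comes off after 24 hours, so T2 (at most 90 minutes after the second ECT) falls while the patch is still worn. Complaints that start later that day or overnight have no scheduled rating in period 1. In period 2 the same complaints are picked up at T6. The check before the third ECT does not close the gap, because by then the next patch was already applied the evening before. A late period-1 effect could therefore be recorded against the other treatment.

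**Working it through.** The article gives no figure to reproduce here. The check sets the sections side by side and counts Table 1 cells.

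**1. Seizure threshold**
- Listed as a measure of rivastigmine's effect: yes (Secondary outcome measures).
- Determination described: titration in the first session of the ECT course (ECT procedure).
- Order of events: first ECT, then weekly screening, then delirium or an MMSE drop, then randomisation, then T1 to T6. The titration precedes randomisation.
- Determinations described within the trial: none in period 1 and none in period 2.
- If the first-session value S is all there is, the within-patient contrast is S − S = 0 for every patient, whatever rivastigmine does.

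**2. Muscle relaxation**
- Aim stated: yes (Introduction).
- Measures listed: blood pressure, peak heart rate, EEG and motor seizure length, postictal suppression index, seizure threshold. None measures muscle relaxation; motor duration describes the seizure.
- Table 1 rows naming it: none.

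**3. Side-effects, with periods T0–T3 and T3–T6**

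| | Within 90 min of 1st ECT of period | Within 90 min of 2nd ECT of period | Day after 2nd ECT of period | Post-patch ratings |
|---|---|---|---|---|
| Period 1 | T1: yes | T2: yes | T3: no | 2 |
| Period 2 | T4: yes | T5: yes | T6: yes | 3 |

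T0 precedes the first trial ECT and serves as the starting value.

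For the 30 completers planned, assume an even split between sequences (15 and 15; the article does not print the ratio):
- Rivastigmine ratings: 15 × 2 + 15 × 3 = 75.
- Placebo ratings: 15 × 3 + 15 × 2 = 75.
- Day-after ratings: 15 under rivastigmine and 15 under placebo, all in period 2, where a rating at both T3 and T6 would give 30 and 30.
- Matched ratings (T1/T2 against T4/T5): 30 × 2 = 60 under each treatment.

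So the totals balance across treatments. Within a patient, the second treatment gets one more chance to show a side-effect. Misattribution moves a late rivastigmine complaint into the placebo count in one sequence, and a late placebo complaint into the rivastigmine count in the other. Both shifts tend to shrink the observed difference.

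**4. Dependence on period length.** The 2-against-3 count rests on two sessions per treatment. If an arm really had four sessions and Table 1 described one arm, the T3 gap would fall inside both arms alike and would not be an imbalance between treatments. The primary outcome definition and Data analysis do not fit that reading. Parts 1 and 2 do not depend on it.

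**The case against.** A reader might infer that none of the three safety questions can be answered. The documents do not support that.

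- **Side-effects.** T1/T2 and T4/T5 are taken at the same time relative to ECT, with the patch on. Order is randomised, adverse events are recorded throughout the trial, and there is a check before each session. A rivastigmine-placebo comparison is available. This objection stands, and it reduces the third part to an imbalance with some possible misattribution.
- **Threshold.** The ECT procedure section describes the course in general and does not say that titration happens only once. The anesthesiologist is said to record threshold, and ECT characteristics are scheduled at all four trial sessions. To say that no on-treatment value exists would be an inference from silence in a condensed article. What stands is narrower: none is described, and the one that is described cannot serve the stated purpose. The wider aim on ECT parameters is still covered by the other listed measures.
- **Muscle relaxation.** The ECT characteristics row is not itemised and the full protocol is not shown, so a measure may exist there. The article nevertheless itemises its measures in the text, and none of them matches this aim.
- **Medication use.** Table 1 also leaves T3 blank for medication use, which might look like a second gap. The treatment allocation section has medication changes registered after every ECT session, so it is not one.
- **Timing of the side-effect check.** The pre-session check is tied to stopping participation and may be separate from the post-ECT rating in Table 1. The article does not say, so this calls for clarification and is not a proven contradiction.

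**Conclusion.** The point holds in a limited form. Two named safety quantities, seizure threshold and muscle relaxation, have no described measurement within the trial periods that could answer the question set for them. The side-effect schedule is unbalanced, with 2 post-patch ratings in period 1 against 3 in period 2, but the side-effect question remains answerable.

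The assumptions are that the first-session titration is the only threshold determination, since no other is described, and, for the side-effect count alone, that each treatment covers two ECT sessions. The primary outcome and the sample size are untouched. These corrections should be made, but they do not threaten the trial's main conclusion.

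**What to change.** 1. **Seizure threshold.** Remove it as a comparative trial outcome and rely on seizure length and postictal suppression index, already scheduled at T1, T2, T4 and T5; or, if an on-treatment determination exists, state when and how it is made. The cost is a text edit. One limit to state: the article says that Thymatron-derived measures are unavailable at sites using the other device. Delivered charge is a poor substitute, because the ECT team sets it.

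2. **Muscle relaxation.** Name a measure already available from the anesthesia record and add it to Table 1, or delete the aim. The article does not show what that record contains, so the sponsor should check this first. If nothing suitable is recorded, deletion costs nothing.

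3. **Side-effects.** Add the side-effect scale at T3. Seven instruments are already given at that visit (DRS-R-98, MMSE, letter fluency, Clock Drawing Test, MADRS, AES and CORE), so the addition is about a minute per patient. The article assigns the DRS-R-98 to a research nurse and side-effects to a research assistant, so staffing at T3 should be confirmed. If the schedule cannot change, specify that the treatment comparison uses T1/T2 against T4/T5, with T6 reported descriptively. The cost is the loss of day-after information.

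4. **Reconcile.** Bring the treatment allocation section (four sessions per arm) and Data analysis (two sessions per treatment) into agreement. State whether the side-effect check before each session and the post-ECT rating in Table 1 are one assessment or two.
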